### Sample size and justification

The primary objective of the study is to determine whether there are meaningful changes in tinnitus outcomes following cochlear implantation in adults with bilateral severe-to-profound hearing loss. Therefore, the study is powered on the Tinnitus Functional Index (TFI) as primary tinnitus outcome measure. The minimum difference on the TFI has not been estimated in the present population and it is not possible to estimate the sample size directly. Previous data on the performance of the TFI in the general UK population suggest an average TFI score of 50.8 (standard deviation = 25.1), and a minimum difference of 17.9 points to improve tinnitus from being perceived as a moderate to a small problem – which could be considered as a meaningful change from a tinnitus severity category considered as bothersome to its lowest self-reported category (Fackrell et al. 2018). Therefore, assuming the average and standard deviation estimates reported above, and a weak correlation of r = 0.3 between the pre- and post-implantation TFI scores, a conservative estimate based on a one-tailed t-test at a significance level of 0.05 suggests that a sample of 31 patients would be required to detect the minimum improvement on TFI that would be meaningful to patients. Considering a very conservative attrition rate of 38% (Fackrell et al. 2018), about 50 patients with tinnitus would be needed to detect a minimum reduction in TFI score post-implantation. This large, conservative, attrition rate has been used due to the new patient-led method of data collection using online questionnaires.

The secondary objectives include exploring new incidence of tinnitus post implantation and factors such as psychological well-being that may distinguish patients with and without tinnitus in this population. Therefore, patients without tinnitus undergoing cochlear implantation will be also recruited. Estimates of prevalence of tinnitus in this population vary with population-based studies and reviews suggesting a prevalence of at least 50% and as high as 80% on average (Baguley & Atlas 2007; Pierzycki et al. 2016). Considering the uncertainty about the true prevalence of tinnitus in candidates for cochlear implantation and potential disruptions to the service due to Covid-19, recruitment will continue after reaching the minimum target of 50 patients with tinnitus to maximise the sensitivity of the study. Recruitment will continue to recruit as many patients as possible within the duration of the study that will enable following up patients for at least 3 months.

# ADVERSE EVENTS

The occurrence of an adverse event specifically as a result of participation within this study is not expected and no adverse event data will be collected.

# ETHICAL AND REGULATORY ASPECTS

Participants and NHS staff will follow COVID-19 safety procedures and infection control measures set out by the cochlear implantation service providers in line with the guidance from Public Health England.

There are no specific risks associated with the research activities. Study questionnaires will be completed by participants remotely, outside of clinical appointments. The frequency and the time required to complete the questionnaires will reduce with time and experience and will not place an appreciable burden on participants or affect their care. There will be no direct benefits to participants from taking part in the study. Voucher payments will be paid to participants as an inconvenience allowance for their time completing study assessments at their final assessment. However, the results will help to inform the design of future trials evaluating the effectiveness of cochlear implantation for the alleviation of tinnitus, which could provide benefits to other patients in the future.

The study will use standard questionnaires and monitoring questions used in research and clinical setting that ask participants about tinnitus and related case history, hearing and listening abilities and psychological well-being. The questionnaires will not provide participants with assessment scores or clinical diagnoses. However, the questionnaires may potentially raise the awareness of participant’s tinnitus, related health conditions, and psychological symptoms. Contact details to British Tinnitus Association help line will be provided in the participant information sheet should the participant wish to seek advice about their tinnitus and related symptoms. Seeking help for tinnitus and access to tinnitus interventions will be also monitored during the study as part of the questionnaire to characterise their potential influence on changes in tinnitus and related outcomes.

The system will use secure data capture methods (e.g. dedicated questionnaire invites) and electronic study forms with password-protected access. The data will be anonymised against the participant identification code and stored on a secure dedicated web server.

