- **Tinnitus case profiling questionnaire (ESiT-SQ)** to comprehensively characterise tinnitus-related socio-demographic, health and lifestyle factors, sound tolerance, tinnitus presence and its characteristics and access to treatments in those who report having tinnitus (Genitsaridi et al. 2019).The full questionnaire will be completed at baseline, while a modified subset of questions will be used at follow up to establish the presence of tinnitus and changes in related characteristics since previous assessment.
- **Tinnitus Functional Index (TFI)** to assess the impact of tinnitus on the patients reporting tinnitus (Meikle et al. 2012). NICE has recommended the TFI for the assessment of tinnitus impact in adults (NICE 2020), and changes on TFI will be used to address the primary objective of the study. Participants who do not experience tinnitus will not complete this questionnaire.

.

- **Patient Health Questionnaire (PHQ-9)** to assess the presence and severity of depressive symptoms (Kroenke et al. 2001). The PHQ-9 is a standard diagnostic questionnaire widely used in both clinical settings and research studies, including assessments of depressive symptoms in patients with tinnitus (Wallhausser-Franke et al. 2017; Aazh & Moore 2019).
- **Generalized Anxiety Disorder (GAD-7)** to assess the presence and severity of anxiety symptoms (Spitzer et al. 2006). The GAD-7 is a standard diagnostic questionnaire widely used in both clinical settings and research including studies assessing anxiety in the general tinnitus population (Aazh & Moore 2019), and cochlear implant recipients (Olze et al. 2011; Bruggemann et al. 2017).
- **Insomnia Severity Index (ISI)** to assess the presence, severity and nature of insomnia symptoms (Bastien et al. 2001). The ISI has been found to be a reliable measure for detecting clinically abnormal insomnia symptoms (Smith & Wegener 2001; 2003; Gagnon et al. 2013). It has been widely used in studies investigating insomnia in the general tinnitus population (Miguel et al. 2014; Cronlein et al. 2016; Aazh & Moore 2019), cochlear implant recipients (Pierzycki & Kitterick 2021), and clinical trials evaluating effectiveness of interventions for insomnia (Curtis et al. 2021).

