- **Two Quality of Life (QoL) questionnaires** to assess changes in (a) hearing-related quality of life using the Health Utilities Index Mark 3 (Feeny et al. 1995) and (b) health-related quality of life using the EuroQol EQ-5D-5L questionnaire (Herdman et al. 2011). Both questionnaires will be used as Health Utilities Index Mark 3 is used by NICE in recommendations for the provision of cochlear implantation in the UK (NICE 2019a), while EQ-5D is the preferred instrument by NICE to measure health-related quality of life with the ‘5L’ version supported for use in prospective clinical studies (NICE 2013, 2019b). The EQ-5D has been also shown to be sensitive to changes in tinnitus and recommended for evaluating interventions intended to alleviate tinnitus (Summerfield et al. 2019).
- **Speech, Spatial and Qualities 12 (SSQ-12)** to assess hearing function in everyday situations (Noble et al. 2013). The SSQ has been found to be sensitive for detecting listening difficulties associated with changes in the severity of hearing loss in the general population (Gatehouse & Noble 2004; Singh & Pichora-Fuller 2010), and an efficient and sensitive measure of changes in self-reported hearing function in cochlear implant recipients (Wyss et al. 2019).

| Figure 1. Study flow chart. |
| --- |
| [figure not shown] |

Table 1. Schedule of online questionnaires.

| **Assessment**  * if tinnitus present  CI = cochlear implant | **Baseline** | **Follow up** | | | | |
| --- | --- | --- | --- | --- | --- | --- |
|  | **pre CI surgery** | **2 weeks post CI surgery** | **CI activation** | **1 month post CI activation** | **3 months post CI activation** | **6 months post CI activation** |
| **Recruitment** |  |  |  |  |  |  |
| Digital consent & contact form | X |  |  |  |  |  |
|  |  |  |  |  |  |  |
| **Tinnitus case profiling questionnaire** |  |  |  |  |  |  |
| ESiT-SQ (Part A & B*) | X |  |  |  |  |  |
| **Tinnitus impact (primary outcome)** |  |  |  |  |  |  |
| Tinnitus Functional Index* | X | X | X | X | X | X |
|  |  |  |  |  |  |  |
| **Psychological symptoms** |  |  |  |  |  |  |
| Patient Health Questionnaire 9 | X | X |  | X | X | X |
| Generalized Anxiety Disorder 7 | X | X |  | X | X | X |
| Insomnia Severity Index | X | X |  | X | X | X |
|  |  |  |  |  |  |  |
| **Quality of life** |  |  |  |  |  |  |
| EuroQoL EQ-5D-5L | X |  |  |  | X | X |
| Health Utilities Index Mark 3 | X |  |  |  | X | X |
|  |  |  |  |  |  |  |
| **Hearing function** |  |  |  |  |  |  |

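### The only support service named for psychological symptoms raised by the questionnaires is a tinnitus helpline, although participants without tinnitus also complete PHQ-9, GAD-7 and ISI

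*Protocol*

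**What the plan says.** The protocol's section "Contact details to British Tinnitus Association help line will be provided in the participant information sheet" comes from is Ethical and Regulatory Aspects. That section makes four relevant statements:

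- The setting is remote: "Study questionnaires will be completed by participants remotely, outside of clinical appointments".
- No results are returned: "The questionnaires will not provide participants with assessment scores or clinical diagnoses".
- The effect on participants is recognised: "the questionnaires may potentially raise the awareness of participant’s tinnitus, related health conditions, and psychological symptoms".
- The response to that effect is the helpline, offered "should the participant wish to seek advice about their tinnitus and related symptoms".

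The sentence after that, on monitoring of help-seeking, also concerns tinnitus only.

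Who answers what is set out under Study Regimen, Online questionnaires. For the TFI the protocol says "Participants who do not experience tinnitus will not complete this questionnaire". In Table 1 an asterisk marks the items given only when tinnitus is present. The row "Patient Health Questionnaire 9" has no asterisk, and neither do the GAD-7 and ISI rows. All three are scheduled at baseline, at 2 weeks after surgery, and at 1, 3 and 6 months after activation.

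The Sample size and justification section says that patients without tinnitus will be recruited, partly to study psychological well-being as a factor that may separate the two groups. The Rationale for the types of information to be collected says that abnormal anxiety, depression and insomnia are found in implantation patients who have no tinnitus, and uses this to justify measuring both groups.

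**The concern.** The protocol foresees a side effect of its own questionnaires and offers a remedy, but the remedy is framed for only part of the people exposed. A participant with no tinnitus who becomes aware of low mood, anxiety or poor sleep while completing PHQ-9, GAD-7 or ISI is directed, as the text stands, to a service for a condition that they do not have. This group is not incidental. It is recruited on purpose, and the protocol itself says that such symptoms occur in it.

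What is at stake is participant safety and the fit between a stated risk and its stated mitigation. No estimate, test or sample size depends on it.

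**Working it through.** The protocol gives no figure for this point, so there is none to reproduce. The check is mainly a comparison of sections, followed by a short calculation of how many participants fall outside the helpline's stated scope.

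**Comparison**

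1. Effect recognised: greater awareness of psychological symptoms (Ethical and Regulatory Aspects).
2. Support named: a tinnitus helpline, for tinnitus and symptoms related to it (same section). No other support service is named in the visible protocol.
3. People exposed: everyone. Table 1 restricts the TFI and Part B of the ESiT-SQ to those with tinnitus, but not PHQ-9, GAD-7 or ISI. The synopsis lists these three under tinnitus-related psychological symptoms, which could suggest a narrower use. Table 1 and the rationale section show that both groups complete them.
4. Symptoms expected outside the helpline's scope: yes, according to the rationale section.

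Steps 2 to 4 do not fit together for participants without tinnitus.

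**Size of the group (illustrative)**

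Inputs: a minimum of 50 participants with tinnitus, and a prevalence of 50% to 80% among implant candidates (Sample size and justification).

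- Total recruited = 50 / prevalence. At 80%: 50 / 0.80 = 62.5, rounded up to 63. At 50%: 50 / 0.50 = 100.
- Without tinnitus = total − 50. At 80%: 63 − 50 = 13. At 50%: 100 − 50 = 50.

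**Scheduled exposure, per instrument**

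- Five sessions: 5 × 13 = 65 to 5 × 50 = 250 responses.
- If all were followed only to the 3-month visit, there would be four sessions: 4 × 13 = 52 to 4 × 50 = 200.
- With five sessions and 38% missing at each (borrowing the attrition rate from the sample size section): 65 × 0.62 = 40 to 250 × 0.62 = 155.

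These are counts of questionnaires, not of people with symptoms. The protocol gives no symptom rate for patients without tinnitus, so the number affected cannot be derived.

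**The case against.** The strongest reply is that the support contacts belong in the participant information sheet, which is not shown. The helpline sentence reports one thing that the sheet will contain and does not say that the list is complete. Some protocol text was also removed before publication. Participants are under the care of an implant team with routine appointments, they have the Chief Investigator's contact details, and the protocol and sheet need a favourable ethics opinion before the study starts. All of this stands. It makes the recommendation conditional and keeps it small, but it does not make the sentence in the protocol fit participants without tinnitus.

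A reader might go further and infer that the protocol has no means of dealing with risk, or that nobody looks at the answers. The documents do not support this. The Statement of Confidentiality says that if a risk of harm is disclosed, the researcher discusses it with the Chief Investigator and reports where appropriate. It also allows medical information to go to the medical team. Answers can be traced, because "The data will be anonymised against the participant identification code" and the Case Report Forms section keeps a separate contact record. The Study Data section has the Chief Investigator monitoring data throughout. That is a data-quality activity and not screening for risk, but it means that one cannot assert from the visible text that answers go unread. Whether, when and by whom they are read for risk is operational detail that the visible text leaves open. What participants believe about this cannot be established from the protocol.

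**Conclusion.** The point holds as a cheap improvement. The support service named in the protocol does not match the population that completes PHQ-9, GAD-7 and ISI. The part outside its scope is about 13 to 50 participants at the minimum recruitment target.

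That range assumes that the recruited mix follows the protocol's 50% to 80% prevalence and that recruitment stops at 50 participants with tinnitus. The protocol intends to continue beyond 50, so the group could be larger. No number of affected people is claimed. The symptom rates in the rationale section are for implant users with tinnitus, so they do not measure this mismatch.

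The conclusion is conditional on the participant information sheet. If the sheet already lists general support for everyone, only the protocol sentence needs to be brought into line. The sample size and the analysis are unaffected.

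**What to change.** In Ethical and Regulatory Aspects, and in the participant information sheet unless it already does so:

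- Add general mood and crisis contacts (for example the GP and an urgent mental-health line) beside the tinnitus helpline, and address them to all participants, with or without tinnitus.
- Tell participants to use those contacts, and not the questionnaire, if they need urgent help.

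The existing rule in the Statement of Confidentiality can stay as it is for any risk of harm that study staff become aware of. If the sponsor adds a sentence on whether answers are reviewed, it should describe actual practice. A flat statement that they are not reviewed should not be inserted unless it is true.

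The cost is wording. The change may need ethics committee review before use (Ethics Committee and Regulatory Approvals). If it is judged to affect participation, continuing consent would also be needed (Informed consent). It adds no patients, visits, data collection or score review.

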| Speech, Spatial, Qualities 12 | X |  |  |  | X | X |
|  |  |  |  |  |  |  |
| **Tinnitus presence & characteristics* follow up** |  |  |  |  |  |  |
| ESiT-SQ (subset) |  | X | X | X | X | X |

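### The plan monitors tinnitus help-seeking and treatment as an influence on change, but as described the follow-up treatment questions appear to be skipped once a participant reports no tinnitus, so these data would be selectively missing where tinnitus resolved.

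*Protocol*

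**What the plan says.** Under Ethical and Regulatory Aspects, the protocol commits to collecting co-treatment data for an analytic reason: "Seeking help for tinnitus and access to tinnitus interventions will be also monitored during the study as part of the questionnaire". The same sentence says the aim is to describe what part this care may play in changes in tinnitus and related outcomes. That section also accepts that the questionnaires may make participants more aware of their tinnitus, and says that a helpline contact is supplied.

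The instrument described as covering tinnitus care is the ESiT-SQ (Synopsis; Study Regimen, Online questionnaires). Its treatment content is described as "access to treatments in those who report having tinnitus". The full version is given at baseline. After that, "a modified subset of questions will be used at follow up to establish the presence of tinnitus and changes in related characteristics since previous assessment".

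Table 1 defines an asterisk as "if tinnitus present". At baseline it stands on Part B of the entry "ESiT-SQ (Part A & B", with Part A unmarked. For the five follow-up assessments the relevant heading is "Tinnitus presence & characteristics* follow up": presence is unmarked and characteristics carry the asterisk. Neither the text nor the table names a treatment or help-seeking item for someone without current tinnitus.

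**The concern.** This is a single-group, before-and-after observational study. Other tinnitus care taken up after surgery is a rival explanation for improvement, and the study may itself prompt some of it. The protocol recognises this by promising to monitor such care.

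If the treatment questions appear only when tinnitus is reported, whether the co-treatment is recorded depends on the outcome it is meant to help explain. A participant who began a tinnitus therapy after one assessment and reports no tinnitus at the next would bypass the questions for that interval. One who took the same therapy and still has tinnitus would answer them. Treatment would then tend to look associated with persisting tinnitus and be under-recorded where tinnitus went away. The estimates of access to tinnitus care promised under The need for this type of study would share the gap. No analysis plan can recover an answer that was never requested.

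**Working it through.** The point turns on how the sections fit together. The arithmetic only bounds its scale.

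**Who is asked, section by section**

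1. Ethical and Regulatory Aspects: help-seeking and interventions are monitored during the study by questionnaire. No tinnitus-present condition is stated.
2. Online questionnaires, ESiT-SQ entry: treatment questions go to those reporting tinnitus.
3. Same entry, follow-up version: presence of tinnitus, and change in related characteristics since the previous assessment. Treatment items are not named.
4. Table 1, follow-up rows: only presence is unconditional.

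Items 2 to 4 together suggest that a tinnitus-free participant at a follow-up answers the presence question and nothing more on this subject. Item 1 needs information from that participant. The two do not fit unless an unlisted, unconditional item exists.

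**What is lost on that reading**

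A participant with tinnitus at baseline is asked about treatment then, and again at each follow-up while tinnitus is present. The gap is care taken up after the last assessment with tinnitus. Follow-ups fall at 2 weeks after surgery, at activation, and about 1, 3 and 6 months after activation. The gap can therefore span about 3 − 1 = 2 months or 6 − 3 = 3 months late in follow-up, and longer once a participant stays tinnitus-free. The stretch from baseline to the first post-operative questionnaire can exceed 3 months, because the repeat baseline is optional.

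**Rough scale**

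Inputs from the protocol:
- tinnitus before implantation: 50% to 80% (Sample size and justification);
- tinnitus after implantation: about 50% (Rationale for the types of information to be collected);
- target with tinnitus: about 50. This reproduces from the protocol's own inputs: 31 / (1 − 0.38) = 50.

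Net proportion no longer reporting tinnitus = (before − after) / before.
- Before = 50%: (0.50 − 0.50) / 0.50 = 0, so 0 of 50.
- Before = 80%: (0.80 − 0.50) / 0.80 = 0.375, and 0.375 × 50 = 18.75, about 19 of 50.

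These prevalences are cross-sectional and come from different sources. The result is a net difference in which new cases offset resolved ones, not a paired resolution rate. It indicates how many could be tinnitus-free at a visit. The number with unrecorded treatment is smaller, because it also requires care taken up after the last tinnitus-positive questionnaire. The protocol gives no uptake rate, so that number cannot be computed.

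**The case against.** The strongest reply is that routing visit by visit is never stated. The phrase limiting treatment questions to people with tinnitus describes the ESiT-SQ as a whole, which is given in full only at baseline. The follow-up items are not listed, and the asterisk sits on characteristics, not treatment. The monitoring commitment carries no condition and sits beside a mention of additional monitoring questions. An unconditional follow-up item is therefore not excluded. The protocol also provides for extraction of data from patient records. All of this stands, and it is why the routing is called an inference here. It does not close the gap. No such item is described, the commitment names the questionnaire as the route, and the clinical topics listed under Rationale are surgery, device use and programming.

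It is also true that the TFI is completed only by participants with tinnitus. On this reading, any visit with a TFI score is one where the treatment questions would be asked. The gap falls on visits without a score. Those visits still matter, because resolution is itself a change in tinnitus that the study sets out to describe and explain.

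Three stronger readings are tempting, and the document does not support them.

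- A reader might infer that people whose tinnitus resolves are never asked about treatment. They are asked at baseline if they have tinnitus then and, on the same reading, at every follow-up until it goes.
- A reader might infer that treatment is recorded only in non-responders. Someone whose TFI falls by the meaningful 17.9 points but who still has tinnitus is a responder and is asked.
- A reader might assume 20% uptake, giving 0.20 × 50 = 10 treated and 0.20 × 19 = 3.8 resolved and treated, and conclude that about 4 of 10 treated participants go unrecorded. The 20% is not in the protocol, and the 19 is the top of a net cross-sectional range. The result also requires that no treated participant had a tinnitus-positive assessment after starting treatment. It is at most an upper bound for that scenario.

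Nor does the protocol say that all improvement will be credited to the implant. It frames the work as describing change and exploring associations.

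**Conclusion.** The point holds in limited form. The commitment to monitor help-seeking and treatment as an influence on change does not fit the ESiT-SQ description and Table 1, which on their natural reading stop asking about treatment once tinnitus is absent. Followed as written, that routing makes co-treatment data missing according to the outcome, among participants whose tinnitus resolved and for the period after their last assessment with tinnitus.

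The conclusion rests on the inferred routing and on there being no unlisted, unconditional item. Its size is not derivable: 0 to about 19 of 50 is a rough net range for being tinnitus-free at a visit, and those with unrecorded treatment would be fewer. The direction of the selection does not depend on that range. It deserves a change to the questionnaire and schedule, since a sentence confirming the present routing would leave the data gap in place.

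**What to change.** In the ESiT-SQ entry under Online questionnaires and in Table 1, take help sought for tinnitus and tinnitus treatment received out of the asterisked characteristics and give them their own unmarked row. Ask this at all five follow-ups of every participant, or at least of everyone who reported tinnitus at any earlier assessment. Set the recall period as the time since the participant last completed a study questionnaire, so that a missed session does not leave an uncovered interval. If such an item already exists in the follow-up subset, list it and state who receives it, so that these sections agree with Ethical and Regulatory Aspects.

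The cost is one or two extra questions per follow-up for participants without current tinnitus, plus a change to the online routing and to Table 1.
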